### 3.4 Clinical Procedures

After baseline assessments, a lip and cheek retractor will be placed. The tooth receiving the desensitizing agent will be isolated with cotton rolls and dried with an air jet, with moisture controlled by suction. The assigned product will be applied in two layers with a microbrush and left on the surface for 10 minutes. Light-cured products will be photoactivated for 10 s (LED Radium-cal, SDI Brasil Indústria e Comércio LTDA, São Paulo, Brazil). Afterward, cotton rolls and the retractor will be removed.

At the end of the study, if experimental treatments are ineffective in reducing dentin hypersensitivity, patients will be treated with the product that shows the best results to avoid further complications.

### 3.5 Assessments

DH intensity will be reassessed using the aforementioned scales at 7, 15, and 30 days, as well as 6 and 12 months post-treatment.

### 3.6 Statistical Analyses

The results of DMFT, VPI, GBI indices, and root exposure height will be presented descriptively. Correlation between the sensitivity assessment methods used (CoVAS and VAS) will be analyzed using Spearman's correlation coefficient. Comparisons among treatments at the same evaluation time and among time points within the same treatment will be analyzed using equality tests for two proportions, with a significance level of 5%.

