## **3. Materials and Methods**

### **3.1 Experimental Design**

This will be a parallel, prospective, randomized clinical trial. Only the volunteers will remain blinded to the allocation group (single-blind design).

A sample of 192 teeth with exposed hypersensitive root dentin will be planned, with 48 teeth per group. The study factors will be: (1) desensitizing treatment at four levels

(Table 1): fluoride varnish (positive control, Duraphat – VF); solution containing crystalline bioactive ceramic (Biosilicate® – SS); self-etch adhesive system (Single Bond Universal – SB); and light-cured fluoride varnish (VL); and (2) evaluation times: baseline (prior to treatments), and 7, 15, and 30 days, as well as 6 and 12 months post-treatment. The response variables will be hypersensitivity assessment through the Visual Analog Scale (VAS) and the Computerized Visual Analog Scale (CoVAS).

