### 3.2 Sample Size Calculation and Patient Selection

Sample size was calculated based on a published study using Sigma Plot 12.0 software, with an expected mean difference in cervical dentin hypersensitivity levels (measured by VAS) of 0.210 after six months. Test details: significance level ( $\alpha$ ) = 0.05; test power ( $1-\beta$ ) = 0.80; dropout ( $\beta$ ) = 0.2. The final sample size was determined as 48 teeth per group.

Patients will be recruited from the undergraduate clinic of FOA-UNESP, aged between 20 and 70 years, with at least one root exposure, totaling 192 teeth with DH in non-cavitated root exposures (not requiring restoration), regardless of location in the dental arch. Teeth will be divided into three groups ( $n = 48$  teeth each) with a 5% significance level. Eligibility criteria are described in Table 2.

**Table 1.** Products to be used in the study and their composition according to the manufacturers

| Material                                                                                                                                                                                                                                                                          | Manufacturer                                  | Composition*                                                                                                                                                                           | Application*                                                                                                                                                                             |
|------------------------------------------------------------------------------------------------------------------------------------------------------------------------------------------------------------------------------------------------------------------------------------------|------------------------------------------------------|-----------------------------------------------------------------------------------------------------------------------------------------------------------------------------------------------|-------------------------------------------------------------------------------------------------------------------------------------------------------------------------------------------------|

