|                                                                                                                                                                                                             | -Use of analgesics or anti-inflammatory drugs                                             |

Following the guidelines of the Federal Council of Dentistry for clinical care during the COVID-19 pandemic, the following protocol will be adopted: patients will be scheduled at staggered times to avoid crowding; 70% alcohol solution will be available in waiting areas for hand hygiene; face masks will be mandatory; the clinical environment will be disinfected between appointments from the least contaminated to the most contaminated areas (reflector handle, chair, stool, assistant cart surface, and dental unit, respectively); PVC barriers will be applied to contact surfaces (mechanical buttons, reflector handles, chair backrests and armrests, stool backrest, handpieces, three-way syringe body, and suction tips); all instruments will be disinfected with enzymatic detergent and sterilized.

Researchers will wear impermeable disposable gowns, disposable caps, protective goggles, surgical masks (for non-aerosol procedures), PPF or N95 masks (for aerosol-generating procedures), face shields, and gloves, all changed after each appointment. Regarding air-jet sensitivity testing in root exposures, relative isolation with cotton rolls will be used, and adjacent teeth will be covered with insulating tape (Isotape, TDV Dental, Pomerode, Santa Catarina, Brazil). The stimulus will consist of an air jet delivered by a three-way syringe positioned 1 cm from the cervical region for a maximum of 2 s. Immediately afterward, patients will indicate sensitivity level on the VAS, which consists of a 10 cm horizontal line where pain is scored from 0 to 10 points: 0 = no pain, 1–3 = mild pain, 4–6 = moderate pain, and 7–10 = severe pain. Patients will mark a vertical line across the horizontal scale to indicate DH intensity. The distance in mm from the zero endpoint will be measured with a millimeter ruler. Teeth with at least grade 3 sensitivity on the VAS will be included.

After selection, each patient will receive and sign an informed consent form (in duplicate), detailing study objectives and procedures.

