The CoVAS will then be used by applying a constant air-jet stimulus, 10 mm from the vestibular surface of the teeth, for 15 s. During this period, the patient will record discomfort intensity on a 0–100 scale using a manually controlled potentiometer. Sensitivity analyses (VAS and CoVAS) will be recorded at baseline. All participants will receive a soft-bristle toothbrush and a non-desensitizing toothpaste for use throughout the study.

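### Section 3.6 compares VAS and CoVAS scores with two-proportion tests, which match neither the outcomes, the hypotheses, the sample-size basis nor the repeated measurement of the same teeth

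*Protocol*

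**What the plan says.** Section 3.1 defines the outcomes: "The response variables will be hypersensitivity assessment through the Visual Analog Scale (VAS) and the Computerized Visual Analog Scale (CoVAS"). Section 3.2 describes both as scores. For VAS, "The distance in mm from the zero endpoint will be measured with a millimeter ruler"; for CoVAS, "the patient will record discomfort intensity on a 0–100 scale using a manually controlled potentiometer". The sample size in the same section is computed "with an expected mean difference in cervical dentin hypersensitivity levels (measured by VAS) of 0.210 after six months", so it concerns a difference in means.

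Sections 3.1 and 3.5 schedule both scales on the same teeth at baseline, 7, 15 and 30 days, and 6 and 12 months. Section 2 sets two null hypotheses: (a) no difference among protocols at each time, and (b) no difference across times within a protocol.

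Section 3.6 then states that comparisons among treatments at one time, and those "among time points within the same treatment will be analyzed using equality tests for two proportions", at the 5% level. No other comparative test is named. Spearman's coefficient is used only to relate the two scales to each other.

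**The concern.** A test of two proportions needs a yes/no result per tooth. The protocol's outcomes are scores, and the protocol never says how a score becomes a yes or a no. Left like this, the cut could be chosen after the data are seen. Whatever the cut, information is thrown away, and the analysis no longer answers the mean-based question for which 48 teeth per group was chosen.

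The time comparisons raise a second problem. Under hypothesis (b) the two results being compared come from the same teeth. The standard two-proportion test treats them as independent samples, and section 3.6 names the same test for separate arms and for repeated measurements.

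This is the only efficacy test in the protocol, so both hypotheses depend on it.

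**Working it through.** **1. The plan's own figure.** Inputs from section 3.2: mean VAS difference 0.210, alpha 0.05 (two-sided assumed), power 0.80, 48 teeth per group. No SD is stated, so 48 can be neither reproduced nor refuted. With n = 2(SD/0.210)²(1.96 + 0.84)², n = 48 requires 0.210/SD = 2.80 × √(2/48) = 0.572, that is SD = 0.367 (no allowance for dropout).

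Reading 0.210 as a difference in proportions does not bring the sample size into line with the planned test, except at extreme rates that the protocol does not state. With n = [1.96√(2p̄(1−p̄)) + 0.84√(p₁(1−p₁) + p₂(1−p₂))]²/0.21², before dropout:

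| Proportions | n per group |
|---|---|
| 0.05 v 0.26 | 46 |
| 0.20 v 0.41 | 75 |
| 0.40 v 0.61 | 88 |
| 0.55 v 0.76 | 80 |

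**2. Between arms: power lost by dichotomising.** Assumptions: normal scores with equal SD, 48 evaluable teeth per arm, independent teeth, treatment lowers the score. The effect that a t-test detects with 80% power is d = 0.578 SD (0.572 by the normal approximation in step 1). Each arm is cut at one threshold, the shares above it are compared with the pooled two-proportion z-test, and power is found by simulation (40,000 runs).

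| Analysis | Shares above cut, control v treated | Power |
|---|---|---|
| t-test on the score | – | 80% |
| Cut midway between the means | 0.61 v 0.39 | 62% |
| Cut 1 SD below control mean | 0.84 v 0.66 | 53% |
| Cut 1 SD above control mean | 0.16 v 0.06 | 39% |

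Check of the midway cut by formula: the difference is 0.614 − 0.386 = 0.227 (unrounded shares). The null standard error is √(2 × 0.25/48) = 0.102, and 1.96 × 0.102 = 0.200. The standard error under the alternative is √(2 × 0.614 × 0.386/48) = 0.099. Power = Φ((0.227 − 0.200)/0.099) ≈ 61%. By the sample-size formula with d = 0.572, about 77 teeth per group would be needed to regain 80%.

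**3. Between times: effect of ignoring the pairing.** What matters here is the correlation φ of the yes/no indicators, which is smaller than the correlation ρ of the scores. For a median cut of a normal score, φ = (2/π) arcsin ρ. The independent-samples standard error is too large by the factor 1/√(1−φ), so the test in effect uses the critical value 1.96/√(1−φ). Then

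- true error rate = 2P(Z > 1.96/√(1−φ));
- power, where a correctly paired test of the proportions has 80%, = P(Z > 1.96/√(1−φ) − 2.80).

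| Assumed ρ | φ | Effective critical value | True error rate | Power instead of 80% |
|---|---|---|---|---|
| 0.5 | 0.33 | 2.40 | 1.6% (simulated 1.7%) | 66% |
| 0.7 | 0.49 | 2.75 | 0.6% (simulated 0.7%) | 52% |

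This loss is measured against a paired test of proportions and comes on top of the loss from dichotomising. For example, with true proportions 0.5 v 0.3, 48 teeth and ρ = 0.5, simulation gives about 53% power for the independent two-proportion test, 68% for McNemar's test and 95% for a paired t-test on the score.

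**The case against.** The strongest reply is that a separate analysis plan may define a responder for each scale, and that section 3.6 does not literally exclude a paired test of proportions such as McNemar's. Both points stand as far as they go. For that reason the missing cut is the weaker part of the concern. A responder definition elsewhere would still leave a proportion test set against score outcomes and a sample size built on a mean. Pairing would remain open unless a paired method were also named.

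A second reply is that the power figures do not measure this trial. That is correct. There is no SD, the figures ignore the 20% dropout in section 3.2, and scores truncated by the entry rule ("Teeth with at least grade 3 sensitivity on the VAS will be included") need not be normal. They show relative loss under stated assumptions.

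Several stronger readings are tempting, and the documents do not support them:

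- *The unpaired test inflates false positives over time.* With positive correlation within tooth it does the opposite.
- *The trial is shown to be underpowered.* Without an SD, its absolute power is unknown.
- *The VAS classes are a faulty endpoint.* The bands ("0 = no pain, 1–3 = mild pain, 4–6 = moderate pain, and 7–10 = severe pain") leave some mm readings unassigned, but they describe severity and are never named as the endpoint, so this is peripheral.
- *A two-group test cannot serve four arms and six times.* It can be applied pairwise. That raises multiplicity but does not rule the test out.

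**Conclusion.** The point holds and should be corrected before any analysis. Nothing in the protocol reconciles section 3.6 with the outcomes in sections 3.1 and 3.2, the hypotheses in section 2, or the mean-based sample size. That mismatch follows from the text alone and needs no assumption. That the test ignores pairing is a fair inference from the test named, in its standard form.

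The size is illustrative. Between arms, 80% power on means becomes about 62% at best and 39–53% at cuts 1 SD from the control mean (normal scores, 48 evaluable teeth per arm). Between times, the nominal 5% becomes about 1.7% or 0.6%, and 80% power becomes about 66% or 52%, at score correlations of 0.5 or 0.7 with a median cut. The practical risk is missed differences, together with a cut that the protocol leaves open.

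**What to change.** Replace the comparison sentence in section 3.6 with a linear mixed model for VAS and, separately, for CoVAS, each as a continuous score:

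- **Outcomes:** all six time points, including baseline. Baseline should not enter only as a covariate, because the model would then give no direct baseline-to-follow-up contrast, which hypothesis (b) needs.
- **Fixed effects:** treatment, time, treatment-by-time, and root exposure height, which section 3.3 uses for stratification.
- **Random effects:** patient and tooth.
- **Hypothesis (a):** treatment contrasts at each follow-up, adjusted for baseline, for example by constraining baseline means to be equal across arms.
- **Hypothesis (b):** time contrasts within treatment, including baseline to each follow-up.
- **Reporting:** 95% confidence intervals for all contrasts.

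If scores are badly skewed, use a patient-level bootstrap, or rank-based tests in paired and unpaired form. If a responder proportion is wanted, keep it secondary, with one cut stated in advance and a paired method (McNemar or GEE) for time comparisons.

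The cost is protocol or SAP wording and slightly more analysis work. No new data or patients are needed.

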#### 4. Implementation schedule

| Steps
Months | A | B | C | D | E | F |
|-------------------------------|----------|----------|----------|----------|----------|----------|
| 1                             | X        | X        |          |          |          |          |
| 2                             | X        | X        |          |          |          |          |
| 3                             | X        | X        |          |          |          |          |
| 4                             | X        | X        |          |          |          |          |
| 5                             | X        | X        | X        |          |          |          |
| 6                             | X        |          | X        | X        |          |          |
| 7                             | X        |          |          | X        |          |          |
| 8                             | X        |          |          | X        |          |          |
| 9                             | X        |          |          | X        |          |          |
| 10                            | X        |          |          | X        |          |          |
| 11                            | X        |          |          | X        |          |          |
| 12                            | X        |          |          | X        | X        | X        |
| 13                            | X        |          |          |          | X        | X        |
| 14                            | X        |          |          |          |          | X        |
| 15                            | X        |          |          |          |          | X        |
| 16                            | X        |          |          |          |          | X        |

**Step A** – Bibliographic survey of all studies to search the literature on root exposure, dentin hypersensitivity, and desensitizing treatments used in prospective studies.

**Step B** – Patient selection; initial evaluation; product application; evaluation at 7, 15, and 30 days.

**Step C** – Statistics and data analysis up to 30 days

**Step D** – 6- and 12-month evaluation; tabulation of final data; statistical analyses.

**Step E** – Drafting of the final scientific report

**Step F** – Drafting of scientific articles.

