### 3.3 Baseline Assessments

Patients' oral conditions will be assessed through the Decayed, Missing, and Filled Teeth Index (DMFT), Visible Plaque Index (VPI), and Gingival Bleeding Index (GBI). Next, with a millimeter probe, root exposure height will be measured as the distance between the apical limit of the cemento-enamel junction and the highest point of the free gingival margin. At this stage, the values will not be classified; scores will be established only after the complete sample has been obtained.

Root exposure height and sensitivity scores by VAS will be stratification variables in the randomization process. The tooth will be considered the sampling unit. Eligible teeth will be entered into an Excel spreadsheet according to root exposure height and mean sensitivity score. To ensure a homogeneous distribution of these two factors across study groups, teeth will be ordered by sensitivity scores and divided into two clusters: one with lower scores and the other with higher scores. These clusters will then be subdivided by smaller/larger exposure size, resulting in four groups: (a) lower sensitivity and smaller exposures, (b) lower sensitivity and larger exposures, (c) higher sensitivity and smaller exposures, and (d) higher sensitivity and larger exposures. This stratified randomization method was based on another parallel clinical trial. Stratification will be performed approximately every 48 selected teeth for methodological feasibility.

In cases where experimental treatments do not reduce dentin hypersensitivity, patients will receive the product with the best performance to avoid further damage.

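### The implementation schedule ends the 12-month evaluation and final statistics in month 12, but with products applied in months 1–5 the 12-month visits fall due from the end of month 12 to about the end of month 16 or 17

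*Protocol*

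**What the plan says.** Protocol Section 3.5 sets the follow-up: "DH intensity will be reassessed using the aforementioned scales at 7, 15, and 30 days, as well as 6 and 12 months post-treatment". The Abstract and Section 3.1 give the same time points. Both null hypotheses in Section 2 cover all of them: (a) compares the protocols at each time point, and (b) compares time points within a protocol.

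Section 4 gives a 16-month calendar with these ticks:

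- Step B, "Patient selection; initial evaluation; product application; evaluation at 7, 15, and 30 days": months 1–5.
- Step C, statistics up to 30 days: months 5–6.
- Step D, "6- and 12-month evaluation; tabulation of final data; statistical analyses": months 6–12, and no later month.
- Step E, drafting the final report: months 12–13.
- Step F, drafting articles: months 12–16.

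Two other statements bear on timing. Section 3.1 fixes the size: "A sample of 192 teeth with exposed hypersensitive root dentin will be planned, with 48 teeth per group". Section 3.3 says how teeth are allocated: "Stratification will be performed approximately every 48 selected teeth for methodological feasibility".

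**The concern.** Step B is the only step in which products are applied, and it starts no earlier than month 1. A visit 12 months after application therefore cannot fall before month 12 has ended. Yet Step D places that visit, the final tabulation and the final statistics in or before month 12, and Step E starts the final report in the same month. The calendar and the assessment plan cannot both be followed.

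The 12-month comparisons are at stake. Sections 1 and 2 motivate the trial by the limited long-term effect of existing agents and the need for longer follow-up, and 12 months is the longest follow-up planned. If the calendar governs the work, the final analysis and report are produced when almost none of those readings exist.

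**Working it through.** **Inputs, all from the protocol.** Step B: months 1–5. Step D: months 6–12. Step E: months 12–13. Calendar end: month 16 (all Section 4). Longest follow-up: 12 months after treatment (Section 3.5). Teeth: 192 (Section 3.1).

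**Time axis.** Let month *k* cover elapsed time *k* − 1 to *k*. Step B then covers 0 to 5, and Step D covers 5 to 12. A visit falls at: application time + follow-up time.

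**Latest application.** Step B also contains the 30-day visit. If every 30-day visit falls inside Step B, the last application is at 5 − 30/30.44 = 4.01, about the end of month 4. If application itself runs to the end of Step B, it is at 5.0.

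| Application | Elapsed time | 6-month visit | 12-month visit | Follow-up when Step D closes (12 − application) |
|---|---|---|---|---|
| Day 1 of month 1 | 0.0 | 6.0 | 12.0 | 12.0 |
| Middle of month 1 | 0.5 | 6.5 | 12.5 | 11.5 |
| End of month 1 | 1.0 | 7.0 | 13.0 | 11.0 |
| Last with 30-day visit in Step B | 4.01 | 10.01 | 16.01 | 7.99 |
| End of month 5 | 5.0 | 11.0 | 17.0 | 7.0 |

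**6-month visit.** It falls between 6.0 and 11.0, inside Step D (5 to 12). The conflict concerns the 12-month visit only.

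**12-month visit.** Only a tooth treated on day 1 of month 1 reaches it by elapsed time 12.0, on the boundary itself. That leaves no time for tabulation and statistics, which also belong to Step D. The remaining visits run to about 16.0, or 17.0.

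**Would a visit window rescue it?** The protocol states none, so this is an assumption. Take application spread evenly over 0 to 4.01 and let the visit be made up to *w* days early. The share of teeth whose visit falls inside Step D is (*w*/30.44)/4.01:

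- 0 days: 0%.
- 7 days: 0.230/4.01 = about 6%.
- 14 days: 0.460/4.01 = about 11%.
- 30 days: 0.986/4.01 = about 25%.

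**Effect of allocating in batches.** About 48 teeth are collected before each stratification, so the first application comes some time after selection starts. No accrual rate is given. For illustration only, if 192 teeth were selected evenly over 4 months, that is 192/4 = 48 per month. The first batch would be complete at elapsed time 1.0, and its 12-month visit would fall at 13.0. Batching therefore lowers the shares above, by an amount the protocol does not let one fix.

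**The case against.** The best case for the plan is that the table is an administrative calendar, which also lists a literature survey and article drafting. The text that governs assessments is clear and consistent: in the Abstract, Section 3.1 and Section 3.5 the visit is at 12 months. In practice the calendar may simply slip and the visits be made when due. Randomisation, outcome definitions and tests are untouched. All of this stands, and it makes the repair cheap. It does not reconcile the dates: Section 4 is the protocol's only statement of when final data are tabulated, analysed and reported. Nor is a damaged table a likely explanation. It reads cleanly row by row, Step C fits the end of Step B, and Step D opens just as the first 6-month visits are about to come due.

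A reader might infer several stronger things that the protocol does not support:

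- *No tooth whatever can reach 12 months inside Step D.* A tooth treated on day 1 reaches it exactly as month 12 ends, and an early visit window would admit a minority. Essentially none at exact 12 months is as far as the text goes.
- *The data will be locked without 12-month readings, or visits will be made early and labelled as 12 months.* No database lock and no early visit is mentioned anywhere.
- *All longer-term conclusions fail.* The 6-month visit fits, and the sample size in Section 3.2 rests on six months. Only the 12-month comparisons are exposed.

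**Conclusion.** The schedule is wrong as written: it contradicts the 12-month assessment that the same protocol requires. When Step D closes, essentially none of the 192 teeth has exact 12-month follow-up, and the last treated have about 7–8 months. The 12-month visits extend 4 to 5 months beyond the end of Step D (16 − 12 and 17 − 12). If application runs to the end of month 5, the last ones fall a month after the calendar itself ends.

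Followed literally, the final analysis and report would precede nearly all 12-month readings, and the 12-month part of both null hypotheses would have no support. The conclusion assumes that each row is one calendar month, that product application occurs only in Step B, and that visits are made at or close to their nominal date. An assumed early window of up to 30 days changes the size (at most about a quarter of teeth under even accrual) but not the conclusion. The 6-month comparisons are unaffected.

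**What to change.** In Section 4:

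1. Extend the table and run Step D to at least month 17, so that the last 12-month visits (about the end of month 16) are followed by tabulation and statistics. If application may continue to the end of month 5, run it to month 18.
2. Move Step E, the final report, after Step D.
3. State that the final analysis is run only after the last 12-month visit.

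The cost is a calendar amendment and a final report about 5 months later (the end of Step D moves from month 12 to 17), or about 6 with the later application limit. No visit is added, because the 12-month visit is already planned. Nothing more is needed: the 12-month time point can stay, and articles that rest on earlier data need not wait.
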